#### Recruitment of participants

Participants will be recruited after randomisation of the food pantries. First, users of participating food pantries will be informed by posters and leaflets. In addition, food pantry users will be personally invited by trained study staff.

#### Study procedure

While food pantry users are waiting in line to enter the room where the food is distributed, trained study staff will screen them for inclusion into the study using a checklist. Food pantry users willing to participate will be informed about the aim, the procedure of the study, and data protection measures, by a printed study information sheet. Individuals who are willing to participate will be asked to provide their name and address on a separate form and to complete the informed consent form as well as the questionnaire (t0). Exhaled carbon monoxide will also be measured. To secure blinding during the baseline data assessment, participants will be informed about the allocation of their food pantry on their next visit to the pantry (usually 1 week later) by the project coordinator.

One and 6 months after the intervention, follow up assessments will be conducted by trained staff. Again, participants will be assessed while waiting in line at the food pantry. Each food pantry will be visited twice. Participants who cannot be reached at the food pantry will receive the follow-up questionnaires by post.

Among all participants who complete the follow-up questionnaires, 50 €20 vouchers for either an electronics store or a clothing store will be raffled, irrespective of the participants’ smoking status.

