## Methods / design

### Setting

Both the stakeholder engagement and the cluster randomised controlled trial will be conducted with the charitable organization the “Berliner Tafel” (“Berlin table”). At its start, the “Berliner Tafel” collected surplus foods from retailers and manufacturers and distributed these foods to social organizations such as women’s refuges, kids clubs, and homeless shelters. Since 2004, the “Berliner Tafel” has provided groceries to clients at 45 food pantries mainly located in religious establishments [32]. Those who fulfil the eligibility criteria defined by the “Berliner Tafel”, i.e. have an income at or below the level of the federal unemployment benefit II, are allowed to take groceries such as fresh fruits, vegetables, and bread for a small fee of one or two euros once a week or every second week [33]. Eligible individuals are allocated to one of the food pantries by officials of the “Berliner Tafel”, mostly according to residents’ postal code [33].

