### Procedures

#### Recruitment of the food pantries and randomisation

In consultation with the coordinator of the food pantries, all the “Berliner Tafel” food pantries will be invited to participate in the study by letters of invitation. Personal invitations will follow in case of no response.

Food pantries whose managers agree to participate via written consent will be randomly allocated to the intervention or control group by means of permuted block randomisation with randomly varying block sizes. The intended allocation ratio is 1:1. The randomisation lists will be computer generated. The team member conducting the randomization will be involved neither in recruitment of participants nor in data collection.

Given that participating food pantries will provide rooms for conducting the study for free, the pantries will be entered into a raffle for ten fuel vouchers valued at €50 each.

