#### Blinding

Due to the nature of the treatment conditions, it is impossible to blind the staff and participants throughout the study. However, the baseline assessment will be conducted while participants as well as staff are blinded.

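### Telling each participant the pantry's allocation at their own next visit does not secure blinded recruitment and baseline for anyone enrolled there later

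*Protocol article*

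**What the plan says.** All references are to the protocol article.

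- **Order of events.** Recruitment of participants: "Participants will be recruited after randomisation of the food pantries".
- **Who recruits, and where.** The same section says that "food pantry users will be personally invited by trained study staff". Under Study procedure this happens in the waiting line, where "trained study staff will screen them for inclusion into the study using a checklist".
- **When allocation is disclosed.** Study procedure gives the delay as the means of securing blinding at baseline: "participants will be informed about the allocation of their food pantry on their next visit to the pantry (usually 1 week later"). The person who tells them is the project coordinator.
- **The claim.** Blinding: "the baseline assessment will be conducted while participants as well as staff are blinded". No exception is made for people enrolled later at a pantry.
- **Separation of roles.** Recruitment of the food pantries and randomisation: "The team member conducting the randomization will be involved neither in recruitment of participants nor in data collection".
- **Attendance.** Setting: users collect groceries "for a small fee of one or two euros once a week or every second week".

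**The concern.** In a cluster trial that randomises before it recruits, the comparison is protected only while the people who invite, and the people who decide whether to join, do not know the cluster's arm. A delayed disclosure can provide that protection if it is timed to the cluster. Here it is timed to the person. The first recruit to be told learns something that is equally true of every user still to be enrolled at that pantry.

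The arms are not equally attractive to join. Intervention pantries offer the course and free nicotine replacement. Under the Control section, control pantries receive the programme only after t2, which is itself six months after the programme ends. Smokers ready to quit would have more reason to enrol where the course is offered now, and staff who knew the arm might invite differently.

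The planned analysis would not remove such a difference. The ICC-adjusted chi-square test and the mixed logit model deal with correlation within pantries, not with who was selected into them. The second primary outcome is also measured as a change from the baseline food security level, so an unblinded baseline questionnaire would bear on it directly. Strengths and limitations discusses bias from unblinding only after baseline and does not mention selection at recruitment.

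**Working it through.** This is mainly a question of whether the stated rule delivers the stated claim, so the sections are set side by side first. Arithmetic then serves only as illustration.

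**1. Does the rule secure the claim?**

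- Allocation is a property of the pantry (randomisation section).
- Disclosure happens at the participant's next pantry visit, usually a week after that person's baseline (Study procedure).
- No sentence says that enrolment at a pantry ends before its first participant is told, or that it takes place in one session. The only count of pantry visits, two, stands in the follow-up paragraph.
- The rule therefore protects those enrolled before the first disclosure at their pantry. For anyone enrolled after it, the rule gives no protection.

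**2. Is later enrolment plausible?**

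- Some users attend only every second week (Setting), so a single session would miss part of them. A session a week later would fall when the first recruits are usually being told, at the same place.
- The target per pantry is 26 smokers × 0.50 participation = 13, and 32 × 13 = 416 (Sample size, Abstract). The article itself calls the recruitment of 32 pantries ambitious.
- Overlap is therefore plausible, but no passage requires it.

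**3. How large could the effect be?**

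The planned effect is 10% − 3% = 7 points (Sample size). The two inputs below are assumptions with no source in the documents: the share *s* of recruits enrolled after the first disclosure, and the between-arm difference *d* in quit propensity among them.

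Spurious difference = *s* × *d*:

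| *s* | *d* (points) | *s* × *d* (points) | share of 7 points |
|---|---|---|---|
| 0.25 | 2 | 0.50 | 7% |
| 0.25 | 3 | 0.75 | 11% |
| 0.50 | 2 | 1.00 | 14% |
| 0.50 | 3 | 1.50 | 21% |

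For the false-positive rate, take a true rate of 3% in both arms, 16 × 13 = 208 participants per arm, and a design effect of 1 + (13 − 1) × 0.02 = 1.24. The effective size is 208 / 1.24 = 167.7 per arm. With p₀ = 0.03 and p₁ = 0.03 + *s* × *d*, SE = √[p₀(1 − p₀)/167.7 + p₁(1 − p₁)/167.7], and a two-sided 5% test is assumed:

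- 0.5 points: error about 5.8%
- 1.5 points: error about 11.2%

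Wider assumptions (*s* from 0.25 to 0.75, *d* from 1 to 5 points) give 0.25 to 3.75 points and an error of about 5% to 36%. The spread shows that the assumptions drive the result.

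**The case against.** The strongest reply is that overlap is inferred. If each pantry enrols on a single distribution day, the Study procedure and Blinding sections agree. Strengths and limitations reports that most users come four or more times a month, and the next visit is usually a week later, so one weekly session could reach most of them. The article condenses a fuller protocol in which session logistics may be fixed. The person who randomises is kept out of recruitment and data collection, and the project coordinator does the telling.

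Much of this stands, and it rules out several stronger readings that a reader might infer:

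- *That later recruits are in fact unblinded, or that the two sections contradict each other.* Both need enrolment to run past the first disclosure, and the number of baseline sessions is not given.
- *That reaching 13 of about 26 smokers requires more than one visit.* The 26 is the average number of smokers at each Berlin pantry in an earlier study, and 50% is an assumed participation rate. Neither is a yield per visit.
- *That recruiters know the arm.* No passage says they are told. They could hear it from informed users in the queue, which is a possibility only.
- *That cluster sizes will be unbalanced between arms.* The documents give no input for this.
- *That the bias has a known size.* With a planned control cessation rate of 3%, an assumed gap of 2–3 points is two-thirds to all of that rate.

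What the reply does not remove is the rule itself. The article does more than leave a detail out: it states when disclosure happens, gives that as the means of blinding the baseline, and ties it to the wrong unit.

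**Conclusion.** The concern holds as a gap between rule and claim. Disclosure at each participant's next visit does not ensure a blinded baseline for anyone enrolled at a pantry after its first participants are told, so the unqualified statement under Blinding is not secured and differential recruitment by arm is possible.

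The conclusion rests on the stated order of events, on allocation being common to the pantry, and on the absence of any stated link between disclosure and the close of enrolment. Whether harm follows depends on whether enrolment outlasts the first disclosure, which the article leaves open. The 0.5–1.5 points are an illustration, not an estimate. Selection of motivated quitters would favour the intervention, but the documents do not settle the direction. The sample size is unaffected. The change is worth making because it is cheap and because the planned analysis cannot correct this selection afterwards.

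**What to change.** In Study procedure, replace the per-participant rule with a per-pantry one: allocation is disclosed on one date for each pantry, only after enrolment and all t0 assessments there are complete, and nobody is enrolled at that pantry afterwards. If single-session enrolment is already intended, saying so, with no later enrolment, settles the matter.

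Report the numbers approached, eligible and enrolled by arm. Process evaluation already calculates a participation rate but does not say that it will be split by arm.

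If enrolment must continue after disclosure, qualify the Blinding statement so that it covers only those enrolled before the first disclosure at their pantry, and add selection at recruitment to the limitations.

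The cost is a sentence or two of procedure and a somewhat longer wait before the earliest recruits learn their allocation. Drawing each pantry's allocation only after its recruitment closes would also work, but it complicates the scheduling of trainers and is not needed.

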### Study design

After the pre-study, a pragmatic two-arm cluster randomised controlled trial, targeting approximately 32 food pantries in Berlin, will be conducted. Cluster randomisation is used to minimise the risk of carryover effects from the intervention to the control group. Data among food pantry users will be assessed on the date of study inclusion (t0), 1 month after completing the smoking cessation program (t1), and 6 months after completing the smoking cessation program (t2) (see Fig. 1). The control group will receive the smoking cessation program after the intervention group has completed the program (waiting list control group).

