### Study population

The study population will include users of any of the participating food pantries who reported smoking at least one cigarette or cigarillo per day. Participants must be at least 18 years old and able to sufficiently understand and speak German. Exclusion criteria includes non-smokers and individuals who smoke less than daily as well as individuals who do not use any of the participating food pantries. In addition, individuals who are 17 years of age or less, are unable to understand and speak German, or are illiterate, will also be excluded. Finally, individuals who only use e-cigarettes or tobacco heating systems will be excluded, since the impact of the original “Rauchfrei” program on this form of tobacco consumption is currently unknown.

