### Outcome measures and evaluation

#### Measures

At t0, participants will be asked to complete a survey containing questions on demographics, developed by a previous study among food pantry users in Germany [41]; the Short Form 12 (SF-12) to measure the quality of life [42]; the quantity-frequency index [37]; the Fagerström Test for Nicotine Dependence (FTND) [39, 40]; the Food Insecurity Experience Scale (FIES) [43]; and the future, present-hedonistic and present-fatalistic subscales of the Zimbardo Time Perspective Inventory [44, 45]. At t1 and t2 continuous abstinence will be measured according to the “Russell standard” (“Have you smoked at all since [start date of last attempt to quit]?” “No, not a puff”; “1–5 cigarettes”; “More than 5 cigarettes?”) [46].

In addition, exhaled carbon monoxide will be measured at baseline as well as at t1 and t2. The time points for the measurements are shown in Table 1.

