#### Outcomes

Primary outcomes are continuous smoking abstinence (yes or no; the percentage of participants with continuous smoking abstinence) and increased food security level (the percentage of participants with an improved food security level) 6 months after the treatment has finished. Smoking abstinence is defined as the self-reported continuous smoking cessation (≤ 5 cigarettes since the start date of their last attempt to quit) validated by the exhaled carbon monoxide test (< 10 ppm of carbon monoxide) [46]. Food insecurity is categorised into four groups: food security; mild food insecurity; moderate food insecurity; and severe food insecurity according to the Food and Agriculture Organization of the United Nations [21].

Secondary outcomes at one and 6 months post-intervention include the point prevalence of smoking abstinence, the mean number of cigarettes smoked per day, the mean number of affirmative responses on the FIES, and the health-related quality of life scores.

Time perspective will be investigated as moderator.

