### Statistical analyses

The data will be analysed using the intention-to-treat principle, therefore including all participants irrespective of any dropouts after the baseline assessment. Missing values among the intention-to-treat population will be imputed using the baseline observation carried forward technique.

The mean, standard deviation, minimum and maximum will be given for continuous variables. Frequencies will be given for categorical variables.

To investigate differences between the intervention and the control group, independent t-tests for continuous variables and chi-square tests for categorical variables will be used. To test hypotheses 1 and 2, differences in the prolonged smoking abstinence and food insecurity improvement (the percentage of participants with an improved food security level) between the intervention and control group will be investigated using the chi-square test adjusted for intraclass correlation within clusters [50]. To account for the nesting of participants within the food pantry, mixed models with the logit link function will be used to predict cessation and food security improvement. To test hypothesis 3, a structural equation model will be used [51]. This identifies if the intervention condition predicts smoking cessation (path A), if smoking cessation predicts improvement in food security level (path B), if the intervention condition predicts the improvement in food security level (path C), and if the impact of the intervention condition on the improved food security level will be attenuated when controlling for smoking cessation.

Secondary outcomes will be analyzed accordingly.

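### Postal follow-up cannot supply the 6-month CO reading that primary abstinence requires, so true abstainers followed by post are most naturally counted as smokers

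*Protocol article*

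**What the plan says.** All four statements are in the protocol article.

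- **Outcome (Outcomes).** Primary abstinence is a self-report of no more than five cigarettes since the last quit attempt began, "validated by the exhaled carbon monoxide test" with a reading below 10 ppm. The primary time point is "6 months after completing the smoking cessation program (t2").
- **Schedule (Measures).** The article states that "exhaled carbon monoxide will be measured at baseline as well as at t1 and t2", with no exception.
- **Follow-up route (Study procedure).** Staff assess participants in the pantry queue. "Each food pantry will be visited twice", and it is not clear whether this is in total or per time point. For the rest: "Participants who cannot be reached at the food pantry will receive the follow-up questionnaires by post".
- **Missing data (Statistical analyses).** "Missing values among the intention-to-treat population will be imputed using the baseline observation carried forward technique". Under Study population, participants are pantry users "who reported smoking at least one cigarette or cigarillo per day".

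The article does not say how to classify someone who reports abstinence by post and has no CO reading.

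**The concern.** The outcome definition, the follow-up route and the imputation rule are each stated, but together they leave a gap. The plan creates a group for whom the first primary outcome cannot be observed, and the imputation rule then decides their result. Carried forward on the outcome, the baseline value is daily smoking, so a person who has really stopped enters the analysis as a smoker.

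Power for hypothesis 1 is at stake, and so is the size of the contrast if postal follow-up is more common in one arm. The abstinence variable is also the mediator in hypothesis 3 and carries the same error there. The food security outcome is not affected in this way, because it comes from a questionnaire that can be posted.

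**Working it through.** **Inputs.** From Sample size: cessation 10% (intervention) and 3% (control), 13 participants per cluster, intra-class correlation 0.02, 5% significance level (sidedness not stated), 80% power, 16 clusters per arm. The share of true abstainers without a t2 CO reading, *q*, is not in the article. All values of *q* below are assumptions.

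**The plan's own figure.** The design effect is 1 + (13 − 1) × 0.02 = 1.24. There are 16 × 13 = 208 participants per arm, so the effective n is 208 / 1.24 = 167.7. The two-proportion formula with normal quantiles and a two-sided 5% test gives 38 clusters. The stated 32 is reproduced with a one-sided 5% test and t quantiles (15.1 to 15.4 clusters per arm, rounded up to 16). At 208 per arm:

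- SE = √[(0.10 × 0.90 + 0.03 × 0.97) / 167.7] = 0.02665
- z = 0.07 / 0.02665 = 2.627
- two-sided power = Φ(2.627 − 1.960) = 74.8%; one-sided power = 83.7%

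The gap between 74.8% and 80% is a separate matter. Here 74.8% serves only as the starting point.

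**Equal loss in both arms.** With no CO counted as smoking, the observed rate is p(1 − *q*).

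| *q* | Observed rates | Difference (points) | Risk ratio | Power, two-sided | Power, one-sided |
|---|---|---|---|---|---|
| 0 | 10.0% vs 3.0% | 7.0 | 3.33 | 74.8% | 83.7% |
| 10% | 9.0% vs 2.7% | 6.3 | 3.33 | 69.9% | 79.8% |
| 20% | 8.0% vs 2.4% | 5.6 | 3.33 | 64.4% | 75.3% |
| 30% | 7.0% vs 2.1% | 4.9 | 3.33 | 58.3% | 70.0% |

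**Unequal loss, true rates 10% and 3%.**

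| *q*, intervention / control | Observed rates | Difference (points) | Risk ratio |
|---|---|---|---|
| 30% / 10% | 7.0% vs 2.7% | 4.3 | 2.59 |
| 10% / 30% | 9.0% vs 2.1% | 6.9 | 4.29 |
| 10% / 40% | 9.0% vs 1.8% | 7.2 | 5.00 |

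The risk ratio is inflated whenever the control loss is the larger. The risk difference is inflated only if 0.03 × *q*(control) > 0.10 × *q*(intervention), that is, if the control loss exceeds 3.33 times the intervention loss.

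**Unequal loss with no true effect.** Take 3% abstinence in both arms, the protocol's own control rate, and a two-sided 5% test.

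- CO obtained for 90% of intervention and 60% of control abstainers: observed 2.7% vs 1.8%. SE = √[(0.027 × 0.973 + 0.018 × 0.982) / 167.7] = 0.01619, so z = 0.009 / 0.01619 = 0.556. Rejection rate = Φ(0.556 − 1.960) + Φ(−0.556 − 1.960) = 8.0% + 0.6% = 8.6%.
- CO obtained for 90% and 80%: observed 2.7% vs 2.4%, SE = 0.01721, z = 0.174. Rejection rate = 3.7% + 1.6% = about 5.3%.

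**The case against.** The strongest reply is that the coding is largely settled: without a CO reading the outcome is missing, the baseline value is smoking, and the participant counts as not abstinent. An unvalidated self-report is, by definition, not the outcome. This stands as the most natural reading. It makes the coding conservative within an arm, but it does not restore the lost power or guarantee a conservative contrast.

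A reader might infer three stronger things that the article does not support.

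- **That a baseline CO reading would be carried forward and would falsely validate abstinence.** Light daily smokers are eligible, so a low baseline reading is conceivable, and the text does not exclude this use. Nothing suggests that it is intended. One sentence closes it off.
- **That the trial is biased in favour of the intervention.** Strengths and limitations does anticipate disappointed controls and possible attrition bias, so unequal shares are possible. It does not say that controls will stop collecting food or move to postal replies. Both arms come for food, most users are regular visitors, the raffle is the same for both, and controls receive the program only after t2. The group sessions end six months before t2 and say little about who is in the queue then. A fourfold gap in loss (40% against 10%) has no support in the text. With true rates of 10% and 3% it would move the risk difference only from 7.0 to 7.2 points. False-positive rates of about 11% and 18% arise only if that gap is combined with 5% or 10% abstinence in both arms, against the protocol's 3% for controls.
- **That people whose food security improves will attend less.** The article gives no evidence for this, and pantry eligibility depends on income.

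It can also be said that recall logistics and sensitivity analyses belong in a fuller protocol or SAP. That is fair for the detail. The gap between the stated outcome and the stated follow-up route, however, is in this text.

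**Conclusion.** The point holds in a limited form. As written, the plan cannot observe the first primary outcome at t2 for participants followed only by post, and true abstainers among them are most naturally counted as smokers.

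- With equal loss, the risk ratio is preserved, while the risk difference and power shrink. Two-sided power falls by about 5, 10 and 17 points at assumed losses of 10%, 20% and 30%.
- With unequal loss, the contrast can shift in either direction. This is a possibility, not a prediction. At 3% abstinence in both arms, the false-positive rate runs from about 5.3% (90% against 80% obtained) to about 8.6% (90% against 60%).

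These figures rest on assumed losses, on the planning rates applying equally to postal and in-person participants, and on counting missing CO as smoking. The true size is unknown because the article gives no postal share. The point ranks as a cheap improvement.

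**What to change.** 1. State that only a CO reading taken at the follow-up in question can validate abstinence, that a baseline CO value is never carried forward, and that no reading means not abstinent in the primary analysis.
2. Add a sensitivity analysis of self-reported abstinence regardless of CO. Report by arm how many self-reported abstainers had no reading and how they were followed up. The primary conclusion should not depend on this analysis, because it uses an unverified measure in an unblinded trial.
3. In the posted questionnaire, invite those who report abstinence to give a CO reading at a food collection on a day when study staff are already scheduled at a pantry. State at the same time whether the two visits per pantry are in total or per time point, because this decides which staff days remain for it.

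The cost is a few sentences, one extra analysis, a short invitation and some scheduling. The downside is a second abstinence figure without biochemical validation. Item 3 has to be in place before follow-up starts, because a t2 reading cannot be recovered later.
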